### Secondary outcomes

Based on the combination of self-report and CO levels, these will include:Point abstinence, defined as a self-report of not smoking in the previous 7 days and verified by a CO level of <10 ppm, at week 5, week 12 and week 25Early lapse, defined by a self-report of smoking (even once) after the quit date but having point abstinence at week 5Late lapse, defined by a self-report of smoking (even once) between week 5 and week 12 but showing point abstinence at week 5 and week 12Early relapse, defined by point abstinence at week 5 but a smoking status in later assessmentsLate relapse, defined by point abstinence at week 5 and week 12 but a smoking status at week 25Differences in the point and continuous abstinences, lapses and relapses between exclusive waterpipe smokers and those who combine it with other forms of smoking tobacco

We will also translate the MPSS [17] for use in a Pakistani population. Once translated, the scale will be administered at baseline and week 25. The scale assesses withdrawal symptoms including anxiety, depression, irritability, restlessness, hunger, concentration and sleep. It also assesses the frequency and strength of urges to smoke. As above, we will also translate the LWDS-11, a tobacco-dependence measure [7], to be administered at baseline and week 25. The scale consists of 11 items and four subscales, the first representing nicotine dependence, the second negative reinforcement, the third psychological craving and the fourth positive reinforcement.

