### Primary outcome

As per Russell’s Standard [16], the primary outcome will be self-reported continuous abstinence for at least 6 months (no smoking allowed in the 7 days prior to each of the three assessments) which is biochemically verified by a carbon monoxide (CO) level of <10 ppm measured by Micro CO (Micro Medical Ltd., Rochester, United Kingdom) at week 5, week 12 and week 25. When a participant self-reports abstinence with an elevated CO level of >10 ppm on any of the three assessments, we will use urinary kits for checking cotinine levels in such cases. Depending on the cotinine level findings the participant will be categorized as a smoker or not.

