### Data collection and management (Fig. 1)

**Fig. 1 Fig1:**
[figure not shown]
CONSORT Flow Diagram

All participants will undergo a baseline assessment including demographic variables (e.g., age, sex, ethnicity, socioeconomic status), past and present smoking (all forms), motivation to quit, withdrawal symptoms (MPSS) and dependency assessments (LWDS-11). Information on waterpipe use will also be collected which will include the quantity, duration and frequency of waterpipe tobacco smoked at the baseline. We will also enquire about their knowledge of health risks associated with waterpipe tobacco smoking, attitudes towards waterpipe tobacco smoking, and intention to quit. The use of concomitant medications will also be collected at baseline. Although social support is not directly assessed, whether smoking is permitted inside the home is assessed. Further assessments at weeks 5, 12 and 25 will include current smoking, any changes in smoking patterns, medication-related AEs and CO breath tests. MPSS, LWDS-11, Strength of Urges to Smoke (SUTS) and cotinine urine tests will be carried out at week 25 (Fig. 2). To pay for their travel and subsistence expenses, participants will receive 200 Pakistani Rupees (approximately US$2) at the last follow-up. Those failing to attend will be reminded and asked to at least send their smoking status via text (mobile phone coverage is high in Pakistan). Where possible, a home visit will be arranged to perform CO measurements. In our previous experience of conducting smoking-cessation trials in Pakistan, such strategies have been successful in keeping attrition rates below 10% [13]. Data will still be collected and maintained on those who either discontinue or deviate from treatment protocols to assess fidelity to the treatment. Data will be initially collected in the form of paper-based questionnaires. Containing no participant-identifiable information, these will be kept in a locked cupboard separate from the Consent Forms at the participating hospital. Every week, these will be photocopied and sent over to the central research office through a secure courier service. Once received, data will be entered in a secure trial database managed by the University of York, created using Qualtrics software (Qualtrics, Provo, UT, USA). Paper copies will also be kept secure in a locked cupboard.

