### Sample size

The primary outcome of the study is continuous abstinence for at least 6 months between week 5 and week 25. Our previous data from a clustered randomized trial in 33 centers in Pakistan [13] with 1955 participants gave an estimate of 37% continuous abstinence at 25 weeks for the behavioral support arm of the trial. A difference of an additional 13 percentage points in the varenicline group is the minimum clinically important difference that we are interested in detecting; this is the median difference reported by the trials which looked at the effectiveness of varenicline and were included in the systematic review by Cahill et al. [8]. In order to detect an absolute difference of 13% in the varenicline plus behavioral support versus the placebo plus behavioral support group, with 80% power and 5% significance, 228 patients would be required per arm. Allowing for a 10% dropout, a total of 508 patients will, therefore, need to be recruited into the study.

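### The primary outcome lets urinary cotinine settle an elevated CO reading, but point abstinence at the same visits rests on self-report and CO alone, so a primary success can be non-abstinent in a secondary outcome

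*Protocol article*

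**What the plan says.** **Primary outcome section.** Self-reported abstinence is one "which is biochemically verified by a carbon monoxide (CO) level of <10 ppm" at weeks 5, 12 and 25. A second rule covers conflicting results: "When a participant self-reports abstinence with an elevated CO level of >10 ppm on any of the three assessments, we will use urinary kits". The outcome of that test is decisive: "Depending on the cotinine level findings the participant will be categorized as a smoker or not".

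**Secondary outcomes section.** The list opens with its own basis: "Based on the combination of self-report and CO levels, these will include". Its first item is "Point abstinence, defined as a self-report of not smoking in the previous 7 days and verified by a CO level of <10 ppm", assessed at the same three visits. Both lapse outcomes and both relapse outcomes require point abstinence at week 5; late lapse and late relapse also require it at week 12. Relapse further requires a later *smoking status*, a term the article does not define. Cotinine is not mentioned in this section.

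**Data collection and management section.** CO breath tests are listed for weeks 5, 12 and 25, but for cotinine the text says only that "cotinine urine tests will be carried out at week 25".

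**The concern.** Someone who is continuously abstinent across three visits should be point abstinent at each of them. Under the two rules as written this need not be so, because a failed CO test can be overturned by cotinine for one outcome and not for the other.

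Point abstinence is the first secondary objective, and lapses, relapses and their predictors are the third and fourth. The Statistical analysis section models point abstinence in the same way as the primary outcome and compares both between exclusive waterpipe smokers and those who also smoke other tobacco. These results will be read side by side, so they should rest on the same smoking status.

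**Working it through.** **1. The plan's own figure.** Inputs from the Sample size section: 37% versus 50% (37 plus 13 points), 80% power, 5% significance (taken as two-sided; the article does not say), 10% dropout.

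n = [1.960·√(2·0.435·0.565) + 0.842·√(0.37·0.63 + 0.50·0.50)]² / 0.13² = (1.374 + 0.585)² / 0.0169 ≈ 227.1, rounded up to 228 per arm. Then 228/0.9 = 253.3, rounded up to 254 per arm, 508 in total. Both stated figures reproduce. Neither depends on how point abstinence is defined.

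**2. The two rules for a self-reported abstainer.**

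| Result at a visit | Primary outcome rule | Point abstinence rule |
|---|---|---|
| CO <10 ppm | abstinent | abstinent |
| CO >10 ppm, cotinine positive | smoker | not abstinent |
| CO >10 ppm, cotinine negative | not a smoker | not abstinent |

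Only the last row conflicts.

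**3. Three cases.** Each participant reports no smoking and has CO below 10 ppm at every visit except one, where CO is above 10 ppm and cotinine is negative. All three are primary successes.

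- *Week 5:* not point abstinent at week 5, so excluded from early lapse, late lapse, early relapse and late relapse.
- *Week 12:* not point abstinent at week 12, so excluded from late lapse and late relapse. An early relapser if *smoking status* follows self-report plus CO; not a relapser if it follows cotinine.
- *Week 25:* not point abstinent at week 25. A relapser on the first reading of *smoking status*, not on the second.

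**4. Size, by assumption only.** The documents give no rate of elevated CO with negative cotinine. Let q be that share of continuous abstainers at each visit, equal in both arms and independent across visits. Analysed per arm: 254 × 0.9 ≈ 229. Continuous abstainers: 229 × 0.37 = 84.7 (placebo) and 229 × 0.50 = 114.5 (varenicline).

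- Discordant at one given visit: q
- Discordant at one or more visits: 1 − (1 − q)³
- Relapser if *smoking status* follows CO (passes week 5, fails week 12 or 25): (1 − q)·[1 − (1 − q)²]

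Expected participants, placebo / varenicline:

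| q | One given visit | At least one visit | Relapser on the CO reading |
|---|---|---|---|
| 1% | 0.8 / 1.1 | 2.5 / 3.4 | 1.7 / 2.3 |
| 2% | 1.7 / 2.3 | 5.0 / 6.7 | 3.3 / 4.4 |
| 5% | 4.2 / 5.7 | 12.1 / 16.3 | 7.8 / 10.6 |
| 10% | 8.5 / 11.5 | 23.0 / 31.0 | 14.5 / 19.6 |

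**5. Sensitivity to independence.** If the same people were discordant at every visit, the share affected at least once would fall to q, the first column of counts. All of them would then fail at week 5, and none could meet a relapse definition.

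**6. Aggregate rates at week 25.** Continuous abstinence would exceed point abstinence only if the discordant cases at that visit outnumbered everyone who is point but not continuously abstinent, such as late quitters and people who returned to abstinence. At q = 5% that group would have to be smaller than 4.2 (placebo) or 5.7 (varenicline).

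**The case against.** The best reply is that the Secondary outcomes wording is shorthand. The Abstract gives the primary outcome in the same CO-only form, yet the Primary outcome section applies cotinine to it, so CO-only wording in this article does not by itself rule cotinine out. The cotinine sentence also categorises the participant and is not expressly limited to the primary analysis. On that view status is set once and reused. The article is also condensed, and a per-visit derivation commonly sits in an analysis plan that is not shown.

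Part of this stands. The shorthand reading is possible, and the intention may well have been a single rule. But no sentence says so, the cotinine rule sits under the primary outcome, and the secondary list states its own basis without it. These are two stated rules that disagree, not a detail left for later. If one rule was meant, the secondary wording still needs correcting.

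On relapse the reply is stronger. Relapse depends on *smoking status*, and the only place that says how to classify someone whose self-report and CO disagree is the cotinine sentence. Read that way, a cotinine-negative participant is not a relapser. The point-abstinence mismatch and the week-5 exclusion remain under either reading.

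**Conclusion.** The inconsistency is real at participant level. Whenever a self-reported abstainer has CO above 10 ppm and negative cotinine, the primary outcome and point abstinence disagree at that visit. If the visit is week 5, the person also leaves all four lapse and relapse outcomes. How many people this concerns is unknown and may be few; the counts above rest on assumed values of q, equal rates by arm, independence across visits and 229 analysed per arm.

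A reader might infer three stronger things that the documents do not support:

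- That primary successes will be reported as relapsers. This depends on the undefined *smoking status*.
- That week-25 continuous abstinence will exceed week-25 point abstinence. This is arithmetically possible but unlikely, since point abstinence also admits people who were not abstinent earlier.
- That the main result is compromised. The primary analysis and the sample size do not use the point-abstinence definition.

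It is a definitional conflict of moderate weight, worth settling before the database is locked.

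**What to change.** 1. Derive one verified abstinence status per visit: self-report plus CO, with cotinine deciding when CO is elevated, as the Primary outcome section already provides. The same sentence can place a reading of exactly 10 ppm, which is now neither below nor above the limit.
2. Define *smoking status* by that derivation, and use it for continuous abstinence, point abstinence at weeks 5, 12 and 25, and all lapse and relapse outcomes.
3. Report a CO-only version of continuous and point abstinence as a sensitivity analysis.
4. Reconcile the Data collection and management section, which names cotinine tests only at week 25, with the Primary outcome section, which needs them at any of the three assessments. Without results at weeks 5 and 12, the primary rule itself could not be applied at those visits.

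The cost is a revised paragraph, one derivation rule and a modest amount of sensitivity analysis. No change to the sample size is needed. Testing at weeks 5 and 12 is already implied by the primary outcome, but it should be confirmed as planned rather than assumed from the data collection schedule.

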### Data collection and management (Fig. 1)

**Fig. 1 Fig1:**
[figure not shown]
CONSORT Flow Diagram

All participants will undergo a baseline assessment including demographic variables (e.g., age, sex, ethnicity, socioeconomic status), past and present smoking (all forms), motivation to quit, withdrawal symptoms (MPSS) and dependency assessments (LWDS-11). Information on waterpipe use will also be collected which will include the quantity, duration and frequency of waterpipe tobacco smoked at the baseline. We will also enquire about their knowledge of health risks associated with waterpipe tobacco smoking, attitudes towards waterpipe tobacco smoking, and intention to quit. The use of concomitant medications will also be collected at baseline. Although social support is not directly assessed, whether smoking is permitted inside the home is assessed. Further assessments at weeks 5, 12 and 25 will include current smoking, any changes in smoking patterns, medication-related AEs and CO breath tests. MPSS, LWDS-11, Strength of Urges to Smoke (SUTS) and cotinine urine tests will be carried out at week 25 (Fig. 2). To pay for their travel and subsistence expenses, participants will receive 200 Pakistani Rupees (approximately US$2) at the last follow-up. Those failing to attend will be reminded and asked to at least send their smoking status via text (mobile phone coverage is high in Pakistan). Where possible, a home visit will be arranged to perform CO measurements. In our previous experience of conducting smoking-cessation trials in Pakistan, such strategies have been successful in keeping attrition rates below 10% [13]. Data will still be collected and maintained on those who either discontinue or deviate from treatment protocols to assess fidelity to the treatment. Data will be initially collected in the form of paper-based questionnaires. Containing no participant-identifiable information, these will be kept in a locked cupboard separate from the Consent Forms at the participating hospital. Every week, these will be photocopied and sent over to the central research office through a secure courier service. Once received, data will be entered in a secure trial database managed by the University of York, created using Qualtrics software (Qualtrics, Provo, UT, USA). Paper copies will also be kept secure in a locked cupboard.

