### Varenicline

Participants allocated to the varenicline and behavioral support arm will receive their first week’s supply on the day of trial enrollment. The treatment, in the form of 0.5-mg tablets, will be dosed at 0.5 mg once daily on days 1–3 and 0.5 mg twice daily on days 4–7. Participants will be expected to return at the end of week 1, coinciding with their quit day, at which point they will be dispensed another pack of medication for 11 weeks, with the pill in the form of 1-mg tablets to be taken twice daily for the rest of the treatment duration. Adherence will be monitored at each visit by using a 7-day timeline follow-back and by looking at the tablets left in the bottle. A 7-day timeline follow-back will consist of a set of questions administered at weeks 1, 5 and 12 asking participants if they have taken the prescribed treatment in the previous week by recalling each day of the week. Adherence will be considered “complete” if the participant adheres throughout 12 weeks; and “partial” if adherence is either irregular or not for the entire period. Participants will be asked to record the nature, timing and duration of any adverse events (AEs) with clear guidance on when to stop the medication and when, and how, to report back to the named clinician in the participating hospital. These clinicians would have received the basic training required in this regard.

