### Adverse events

There will be a vigilant surveillance system in place for adverse events (AEs) occurring during the course of the trial with particular emphasis on identifying, recording, reporting and managing serious suspected drug reactions. We will use standard definitions to distinguish between an adverse event (AE), a serious adverse event (SAE) and a serious suspected adverse drug reaction (SSARD).

In the event of any AE reported by the participant, their attendant or health care staff, the research assistant will complete an AE Form, which will include any available medical diagnosis. For reporting SAEs, a form will be provided by Pfizer known as a Pfizer-provided Investigator-initiated Research Serious Adverse Event Form. The Reportable Event Fax Cover Sheet provided by Pfizer will also be included with each SAE submitted. The research assistant will photocopy and complete this form, send it in the post to the central research office and call the trial manager on the same day providing a verbal report of the event. The research assistant will be trained to differentiate between AEs and SAEs. However, the trial manager, who is medically qualified, will ensure that the event is classified appropriately after receiving the verbal report. The trial manager will also code the event using the Medical Dictionary for Regulatory Activities (MedDRA) [18] and cascade the information as follows.

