All AEs must be reported to the principal investigator (Pakistan) within 3 days of detection. AE data will be collated and reported to the trial sponsors and National Bioethics Committee at 6-monthly intervals. These must also be reported to the Study Operational Committee and the Independent Trial Steering Committee at their regular meeting. All AEs that have the potential to develop into SAEs will be followed to resolution or stabilization and reported as SAEs if they become serious. All SAEs must be reported to the principal investigator and Pfizer within 24 h of detection and should also be reported to the trial sponsors and the National Bioethics Committee within three working days. All SSARDs should be reported to the sponsors and the committee within 24 h of the event. All serious events must also be reported to all study investigators and the chair of the Independent Trial Steering Committee (within 3 days for SAEs and within 24 h for SSARDs). If the trial manager requires more detail in relation to any SAEs or SSARDs then they may request the trial statistician to unblind the treatment condition. The chief investigator will have the overall responsibility to ensure that all AEs are reported according to the above protocol.

In addition to assessing seriousness, the trial manager, who is medically qualified, will assess all AE for causality, severity and expectedness. This will be done in consultation with the principal investigator and the event will be classified as follows:Unrelated: when the event is considered not related to the study treatmentPossibly: when an association of the event with the study treatment cannot be ruled outProbably: when temporal association and an absence of any other explanation suggest that the event could be related to the study treatmentDefinitely: based either on known side effects of the study treatment or on challenge testing, a suggestion that the study treatment is the most likely cause of the event

All AEs/SAEs that fall under the possible, probable or definitive category will be classified as adverse reactions or SSADRs.

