The MPSS items will be analyzed individually, summated to give an overall score and scored in three blocks as suggested by West et al. [17]. Similar approaches will be used for the LWDS-11 [7] and SUTS [19] scales. Appropriate regression analysis will be used for each outcome, linear for the summated scores if the assumptions are met, otherwise appropriate measures will be taken, and ordered logistic regression used for the Likert-scale individual items. Analysis of AEs and SAEs will explore whether these differ by treatment arm using chi-square tests. In case of missing data, multiple imputations and appropriate sensitivity analyses will be conducted. As it is likely that more than one variable will have missing data we will use multiple imputations using chained equations (MICE). A minimum of 10 imputations will be performed; however, the final number of imputations will depend on the missing data. We will report the decisions that we make with regard to the number of imputations and the variables we use in the imputations. We will also conduct a sensitivity analysis to explore the implications of the missing-at-random assumption [20, 21]. A significance level of 0.05 will be used for the primary analysis whereas this will be 0.1 for the secondary analyses.

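### The adverse event item at the week 5, 12 and 25 visits is worded as medication-related events, narrower than the all-AE recording, causality and between-arm comparison that it feeds

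*Protocol article*

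**What the plan says.** **Scheduled visits.** The section on data collection and management lists the follow-up content: "Further assessments at weeks 5, 12 and 25 will include current smoking", followed by "any changes in smoking patterns, medication-related AEs and CO breath tests". This is the article's only description of the adverse event item at those visits.

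**Recording by participants.** The Varenicline section says: "Participants will be asked to record the nature, timing and duration of any adverse events (AEs". It sets no limit by suspected cause.

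**Adverse events section.** Four statements bear on scope:
- surveillance: "There will be a vigilant surveillance system in place for adverse events (AEs) occurring during the course of the trial", with particular emphasis on serious suspected drug reactions;
- the trigger for a form: "In the event of any AE reported by the participant, their attendant or health care staff, the research assistant will complete an AE Form";
- onward reporting: "All AEs must be reported to the principal investigator (Pakistan) within 3 days of detection";
- causality: the medically qualified trial manager "will assess all AE for causality, severity and expectedness", consulting the principal investigator, on a scale that runs from unrelated to definitely related.

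**Analysis.** The Statistical analysis section says: "Analysis of AEs and SAEs will explore whether these differ by treatment arm using chi-square tests". It does not restrict the comparison to related events.

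**The concern.** An item confined to medication-related events cannot be answered without a view on cause. At a visit, the people present are the participant and the research assistant. The article gives the causality judgement to others, at a later step, and the only classification training it states for research assistants is telling AEs from SAEs.

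An event set aside at the visit, and not captured another way, is never rated for causality, coded or counted in the comparison by arm. The events most exposed are those with a ready alternative explanation. In a cessation trial these include anxiety, low mood, irritability and poor sleep, which the Secondary outcomes section lists as withdrawal symptoms measured by the MPSS. In a placebo-controlled trial, the randomized comparison is what should show whether such events are commoner on drug. That comparison works best when events enter it without prior sorting by presumed cause.

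**Working it through.** No figure in the article depends on this wording, so the check is a comparison of sections.

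**Step 1: scope at each stage.**

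| Stage | Section | Scope |
|---|---|---|
| Scheduled item, weeks 5, 12 and 25 | Data collection and management | Medication-related AEs |
| Participant's own record | Varenicline | Any AE |
| AE Form | Adverse events | Any AE reported |
| Report to principal investigator | Adverse events | All AEs |
| Causality rating | Adverse events | All AEs, including an unrelated category |
| Comparison by arm | Statistical analysis | AEs and SAEs, no relatedness limit |

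Five of the six rows carry no relatedness filter. The exception is the scheduled item, which is also the only row tied to fixed time points for every participant.

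**Step 2: what happens to an event first thought unrelated.** If the visit item is asked as worded, the event is not elicited by it. It can still arrive in two ways: the participant has recorded it, or the participant, an attendant or health care staff report it. Both routes are open throughout. Neither is described as a uniform question put to everyone at each visit, and the consent procedure allows for participants who cannot write.

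**Step 3: other cover for mood and sleep symptoms.** Treatment lasts 12 weeks (1 week plus 11 weeks). The MPSS is given at baseline and week 25. No listed scale covers these symptoms at weeks 5 and 12, so during treatment the adverse event item is the only listed visit item that would pick them up.

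**Step 4: likely effect on the comparison.** Let p1 and p0 be the true risks of a given type of event in the two arms, and let s be the probability that such an event is recorded. Participants, research assistants and investigators are blinded, so s should be about the same in both arms. The recorded risks are then about s × p1 and s × p0.
- The ratio is unchanged: (s × p1)/(s × p0) = p1/p0.
- The difference shrinks to s × (p1 − p0), and the expected number of events falls by the factor s, so power falls.
- Event types that site staff do not associate with the drug have the lowest s and contribute least to the comparison.

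**Step 5: size.** The article gives no adverse event rates and nothing from which to estimate s, so no loss in events or power can be calculated.

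**The case against.** The strongest reply is that the article, read as a whole, collects all adverse events. The visit list is introduced as things the assessments will include, which is not exclusive. The dedicated Adverse events section sets the procedure and is unfiltered throughout. Its form trigger does not require an unprompted report, so an event mentioned at a visit needs a form whatever its suspected cause. Participants are actively asked to record any event. That request sits in the Varenicline section, but placebo is dispensed in the same way, so it can be read as covering both arms. No sentence tells a research assistant to screen for relatedness, and the adjective may be loose shorthand. The MPSS measures mood and sleep in everyone without attribution, although week 25 falls after treatment has ended. The schedule in Fig. 2 and the visit forms are not shown and may use the broader wording.

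Much of this stands. A reader might infer that visits collect nothing but medication-related events, or that unrelated events are lost altogether. The documents support neither, given the non-exclusive verb and the two open routes. What does not fall away is that the qualifier was written into the only description of the scheduled item. A form built from that sentence would carry it, and it disagrees with every later stage.

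**Conclusion.** The inconsistency is real and should be corrected. The scheduled item is worded more narrowly than the recording, causality and analysis steps it serves. Asked as worded, it moves a judgement of relatedness ahead of the step designed for it.

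The consequence is a risk of under-ascertainment, not a demonstrated failure. A reader might conclude that the comparison of AEs by arm is incomplete or biased. The text does not establish that: unfiltered routes remain, and blinded collection makes the loss probably similar across arms unless side effects reveal allocation. The main risks are fewer recorded events, less power and missed drug effects that nobody recognises as such, chiefly at weeks 5 and 12. Any percentage loss would be a guess.

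This rests on two assumptions: that the visit form follows the printed sentence, and that some events thought unrelated are neither recorded nor reported by another route.

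**What to change.** In the data collection and management section, and in Fig. 2 and the visit form if they say the same, replace the medication-related wording with *all AEs, regardless of suspected relationship*. Put the same question at each of weeks 5, 12 and 25 in both arms. Leave relatedness to the causality assessment already set out in the Adverse events section. Keep the comparison in the Statistical analysis section on all AEs and SAEs, and report related AEs as a subset.

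The cost is one phrase in the protocol and on the form, plus a few more AE forms for research assistants to complete and the trial manager to rate. The sample size, abstinence outcomes and treatment procedures are unaffected.
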